### **G. Urinary $\text{Ca}^{++}$ /Cr ratios**

At each monthly prenatal visit, mothers will provide a urine sample (“clean catch”). Because dehydration can affect urine calcium levels, mothers will be instructed to maintain good hydration throughout their pregnancy. Urine samples will be sent to each Clinical Center’s Clinical Chemistry Laboratory for urinary calcium and creatinine measurement, and the urinary calcium to creatinine ratio will be derived. [name] has used this measure to monitor women on vitamin D supplements in his other trials and has shown that this is the earliest sign of impending toxicity.

If an elevated Ca/Cr ratio is found, the woman will be asked to stop the study pills. An elevated Ca/Cr ratio will be defined as  $\geq 1.55$ , when measured on the mmol scale, or  $\geq 0.55$ , when measured on the mg/mg scale. She will be asked to stop the study medication and to return for a repeat evaluation after being instructed to increase her fluid intake, to ascertain whether this was due to dehydration or true hypercalciuria. If the repeat test is normal she will resume the study medication and continue in the study. If the repeat test remains elevated, she will have further blood tests including serum 25(OH)D levels and calcium level, if these are within normal limits, she will restart her study medication and continue on the study. If her serum 25(OH)D and calcium levels are elevated, she will be withdrawn from study treatment and be further evaluated by her doctor as appropriate. This will be recorded as a serious adverse event. (Please see Section VII. J. for further details).

If there is a subsequent elevated urine Ca:Cr ratio, but it is a lower than the initial elevated urine Ca:Cr ratio, she will be reminded to maintain hydration by drinking water daily, and will continue on her study medication. If the subsequent elevated urine Ca:Cr ratio is greater than the initial elevated ratio, she will be asked to stop her study medication, and reminded to drink non-caffeinated fluid. The woman will return to the clinic center and have a blood draw for serum Ca and 25(OH)D measurement. If these are within normal limits, study medication will resume. If the values of either are out of normal limits, the subject will be withdrawn from study treatment, but continued to be followed under the intention-to-treat paradigm. A serious adverse event will be submitted to the DCC and she will be referred to her physician for follow up treatment.

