## **H. Blinding**

Until the end of the trial, all investigators, clinical staff and participants are masked to trial outcome data, with the exception of the trial statisticians, and the data manager. Due to the nature of the intervention, laboratory technicians and staff obtaining calcium/creatinine ratios may be able to infer treatment group assignment. However, there are other more common causes of elevated calcium/creatinine ratios (i.e. dehydration). Therefore, we do not anticipate any issues with unintentional unblinding of study investigators or clinical staff. There may be a rare case where emergency unblinding may be necessary (e.g. overdose of study pills or persistent elevation of urinary Ca/Cr ratio with hypercalcemia and hypervitaminosis D). In this case, emergency unblinding will occur at the discretion of the DCC and appropriate actions will be taken, including immediate reporting to the DSMB. In cases where non-emergent unblinding may be necessary, The DCC PIs will seek input from the DSMB prior to unblinding.

For quality control purposes, 20% of the blood samples will also be sent to [name] lab for 25 (OH) D measurements. However, we will adhere to established procedures to maintain separation between laboratory staff and clinical staff that have patient contact. For quality assurance, [name] will receive a report of measured 25(OH)D levels that are stripped of all identifying patient information (identifier and clinical information).

To ensure rapid intervention in the unexpected event of out-of-range ( $\geq 1.55$  mmol/mmol) calcium/creatinine ratios, urinary calcium and creatinine measurement will be conducted at each Clinical Center's Clinical Chemistry Laboratory. Again, we will adhere to established procedures to maintain separation between laboratory staff and clinical staff that have patient contact or are responsible for measuring primary or secondary endpoint outcomes. In the event of an out-of-range calcium/creatinine ratio, the patient will be contacted for follow-up, with the procedure detailed in Section I below.

Given the benign treatment intervention, the manufacturing of prenatal vitamins, placebo and Vitamin D supplement by the same drug company (Tishcon Corp), the distribution of study vitamins by the DCC, off-site assays of 25(OH)D levels, protocols to maintain separation

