### **I. Data Safety and Monitoring of Each Subject**

An external Data Safety and Monitoring Board (DSMB), composed of vitamin D metabolism experts, early life asthma experts, obstetricians, an ethicist, and a statistician has been appointed by the NHLBI. The board will be convened prior to study initiation to review the protocol and to examine and comment upon "shell" reports that will be used to illustrate data accumulation as the study proceeds.

All study subjects will be monitored for hypervitaminosis D, the only known toxicity of which is hypercalcemia. Operationally, we will define caution by urinary calcium/creatinine ratio  $\geq 1.55$  mmol/mmol from the samples that are obtained monthly starting 1 month after randomization. Whenever any patient exceeds the caution limit, the study medication will be temporarily discontinued and a specific case study will be initiated. The first elevated urine Ca:Cr ratio will trigger the repeat measure of the urine calcium/creatinine ratio after hydration (drinking at least 8 oz of water prior to coming in for the visit). If the repeat urinary calcium/creatinine after hydration remains elevated, the patient will have serum calcium and vitamin D levels checked at the Clinical Center's Clinical Chemistry Laboratory. If the serum calcium and vitamin D levels are within normal limits, the subject will resume study medication. Predefined cutoff of a calcium of  $\geq 10.2$  mg/dl or vitamin D level of  $\geq 300$  nmol/L are criteria for removal from the study treatment. The subject will still be followed in the intention-to-treat paradigm. Further evaluation (including the possibility of taking additional calcium or vitamin D supplements as well as workup for other disorders such as hyperparathyroidism) will be pursued further depending on the serum calcium and vitamin D levels as appropriate. The appropriate IRB will be notified, and the NIH and FDA will be notified per their protocols. The DSMB chair will be notified, as with any severe adverse event. After the detailed case review has been performed by the clinical center to ascertain the cause of the hypervitaminosis D in the subject and reviewed by the DSMB to make an informed decision about the study's continuation. If the elevated levels in the subject are attributed to the vitamin D supplement, the subject will be withdrawn from supplementation but will continue to be monitored.

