### **J. Adverse Events and Reporting to the DSMB**

- Serious Adverse Events (SAEs) will include the following:
  - Symptomatic hypercalcemia and/or elevated 25(OH)D level (as defined above)
  - Pre-eclampsia and Eclampsia
  - Any hospitalization of mother (including severe pregnancy complications such as HELLP [Hemolytic anemia, Elevated Liver enzymes, Low Platelet count] syndrome, deep vein thrombosis or coagulopathy), except for
    - Delivery after 32 weeks

- Pre-term labor not resulting in delivery
- Any newly diagnosed serious maternal illness
- Maternal death from any cause
- Pre-term delivery <32 weeks gestation
- Discovery of major fetal anomalies or diagnosed major congenital anomalies (note: an elective abortion in the absence of diagnosed congenital anomalies will be considered a study withdrawal, not an SAE)
- Still birth/Intrauterine fetal death
- Neonatal demise
- Any neonatal intensive care admission
- Adverse Events (AEs) will include (but not limited to):
  - Pre term delivery between 32 and 37 weeks
  - Gestational diabetes
  - Gestational hypertension
  - Perinatal infections
  - Anemia
  - Prolonged rupture of the membranes
  - Placental abnormalities such as previa or marginal abruption
  - Meconium staining
  - Abnormal labor
  - Low birth weight (<1500g)
  - Asymptomatic hypercalcemia ( $\geq 10.2$ mg/dl)
  - Hypercalciuria
    - Urine calcium/creatinine ratio  $\geq 1$  after repeat measure. If ratio normalizes after hydration this is NOT an adverse event

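### Section VII.J sets the hypercalciuria adverse event at a ratio of 1 where the rest of the current protocol uses 1.55, and isolated asymptomatic hypercalcemia can be graded two ways

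*Supplement*

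**What the plan says.** All references are to the current protocol unless stated.

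**Urine limit.** VI.G: "An elevated Ca/Cr ratio will be defined as" at least 1.55 on the mmol scale, or at least 0.55 on the mg/mg scale. A first elevated ratio stops the study pills and leads to a repeat after extra fluid. "If the repeat test is normal she will resume the study medication and continue in the study". VII.H uses 1.55 mmol/mmol as its out-of-range value and sends the case on: "In the event of an out-of-range calcium/creatinine ratio, the patient will be contacted for follow-up, with the procedure detailed in Section I below". VII.I uses the same 1.55 as its caution limit, and VIII uses it to start a case study. VII.J lists hypercalciuria among the AEs as a ratio of at least 1, without a unit, "after repeat measure. If ratio normalizes after hydration this is NOT an adverse event".

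**Serum values.** For a first episode whose repeat stays high, VI.G says: "If her serum 25(OH)D and calcium levels are elevated, she will be withdrawn from study treatment", and records an SAE. For a later ratio above the first elevated one it says: "If the values of either are out of normal limits, the subject will be withdrawn from study treatment", and then "A serious adverse event will be submitted to the DCC". VII.I gives the cutoffs for removal from treatment as calcium of at least 10.2 "mg/dl or vitamin D level of" at least 300 nmol/L. VII.J's SAE list has symptomatic hypercalcemia and/or an elevated 25(OH)D level. Its AE list has asymptomatic calcium of 10.2 mg/dl or more.

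**Routes.** Under VII.J an SAE form is to be on the DSMB page within 72 hours of the center's notice to the DCC. AEs go into quarterly reports.

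**The concern.** VII.I calls hypercalcemia the only known toxicity of hypervitaminosis D, and the monthly urine ratio is the trial's screen for it. The events that track this toxicity should have one definition and one grade. Instead, a coordinator working from VII.J can code an AE for a woman whom VI.G calls normal. A coordinator working from VI.G can file an SAE for a finding that VII.J calls an AE. Three centers could then code like cases differently. At stake are the AE and SAE counts shown to the DSMB and the speed at which a case reaches it.

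**Working it through.** **1. The limits side by side.**

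| Section | Limit |
|---|---|
| VI.G | ≥1.55 mmol/mmol, or ≥0.55 mg/mg |
| VII.H | ≥1.55 mmol/mmol |
| VII.I | ≥1.55 mmol/mmol |
| VIII | exceeds 1.55 mmol/mmol |
| VII.J (AE) | ≥1 on repeat, no unit |

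**2. Does VI.G's own pair agree?** The factor from mg/mg to mmol/mmol is the molar mass of creatinine over that of calcium. With assumed physical constants of 113.12 and 40.078 g/mol this is 113.12 / 40.078 = 2.822. Then 0.55 × 2.822 = 1.552, which matches the stated 1.55.

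**3. Can the missing unit reconcile VII.J?** No, on either scale.

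- Read as mmol/mmol: 1.00 / 1.55 = 0.645, so the AE limit is 35% below the action limit. The disputed band is a repeat of 1.00 to 1.54 mmol/mmol. By the protocol's own pair (1.55 / 0.55 = 2.818), that is 1.00 / 2.818 = 0.355 to 1.54 / 2.818 = 0.546 mg/mg.
- Read as mg/mg: 1 × 2.82 = 2.82 mmol/mmol. A repeat of 0.55 to 0.99 mg/mg is then elevated in VI.G but below VII.J's number.

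The first reading is the likelier. The original protocol's limit was 1.0 mmol/mmol (its VII.J, VII.K and VIII). Item 36 of the Summary of Protocol Changes, which raised the limit, lists VI.G, VII.H, VII.I and page 35, but not VII.J. This is an inference about origin; the conflict lies within the current text.

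**4. One woman through the urine rules (illustrative values).** First ratio 1.70, hydrated repeat 1.20 mmol/mmol. Under VI.G 1.20 is below 1.55, so the repeat is normal and she resumes. Under VII.J's first sentence 1.20 is at least 1 on repeat, so it is an AE. Under its second sentence a ratio that normalizes is not an AE. VII.J does not define that word.

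**5. The grade, case by case.** VI.G's normal limits are taken to be VII.I's cutoffs, because VI.G gives no figures.

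| Case | VI.G | VII.J |
|---|---|---|
| First episode, calcium and 25(OH)D both raised | SAE | SAE (25(OH)D raised) |
| First episode, calcium alone, no symptoms | silent: its rule joins the two values by 'and' | AE |
| Later higher ratio, 25(OH)D alone raised | SAE | SAE |
| Later higher ratio, calcium alone, with symptoms | SAE | SAE |
| Later higher ratio, calcium alone, no symptoms | SAE | AE |

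Only the last row gives two different grades. The second row is a gap in VI.G's wording; VII.I's 'or' already covers removal there.

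**The case against.** The best defence is that the sections should be read together. The first-episode repeat is triggered only by a ratio of 1.55 or more, VI.G treats anything below that as normal, and VII.J says a ratio that normalizes is not an AE. On that reading a repeat of 1.00 to 1.54 is excluded, and a repeat of 1.55 or more is an AE under either mmol figure. This largely settles the band for a careful reader. It does not explain why VII.J prints 1, and it relies on a word that VII.J leaves undefined.

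On the grade, it can be said that VI.G governs cases found through the urine pathway and VII.J gives the general category. Nothing in the text says so, and VI.G itself refers the reader to VII.J for further details.

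The case must also be rare: it needs a first elevated ratio, a later one above it, raised calcium, normal 25(OH)D and no symptoms in one woman. Section III reports 347 women who completed the earlier supplementation trial with no episode of toxicity. That stands, and it bounds the importance of the point.

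A reader might infer more, which the documents do not support:

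- **That grading could decide whether the trial stops.** The SAE provision in VII.J concerns an unanticipated difference between arms that is both statistically and clinically significant, uses an adjusted alpha of 0.01, and gives the NHLBI Director a discretionary power. Hypercalcemia is the anticipated toxicity, so it is doubtful that the provision reaches it. VII.K's ground for considering termination requires, besides an excess of adverse events, no evidence of benefit.
- **That the DSMB would not hear of a case.** VII.I notifies its chair on removal from treatment.
- **That a later, higher ratio cannot be recorded because VII.I asks for no repeat urine.** VII.J's AE list is expressly open.

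**Conclusion.** The point holds as an internal inconsistency in the current protocol, and it is a minor correction. VII.J's limit of 1 disagrees with four other sections on either unit. If it is the old mmol/mmol limit, as is likely, it is 35% too low and puts repeats of 1.00 to 1.54 mmol/mmol in doubt. Calcium out of limits alone, without symptoms and with normal 25(OH)D, is an SAE under VI.G's later-episode rule and an AE under VII.J. That changes the route (72 hours or quarterly) and the tally in which it is counted. The grade conflict assumes that VI.G's normal limits are the 10.2 mg/dl and 300 nmol/L of VII.I.

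The number of women affected cannot be computed from the documents; it is probably small. The same rules apply to both arms under blinding, and nothing here shows bias between them. The intention-to-treat analysis of asthma or recurrent wheeze does not use these events.

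**What to change.** 1. **VII.J:** replace the limit of 1 by at least 1.55 mmol/mmol (at least 0.55 mg/mg) on the hydrated repeat, and define 'normalizes' as below that limit.
2. **VI.G and VII.J:** state one grade for isolated asymptomatic hypercalcemia in both. The DSMB should choose it, blind to arm, since the AE and SAE lists were revised on its recommendation (item 27 of the change log). Use VII.I's serum limits, calcium of at least 10.2 mg/dl or 25(OH)D of at least 300 nmol/L, for first and later episodes throughout VI.G.
3. **Recorded events:** re-code to these definitions, blind to arm.

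A later ratio that is still elevated but below the first should not be written out of the AE definition. VII.I's statement that it needs no further action concerns management, not coding.

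The cost is one clarification letter, one DSMB decision and some re-coding at the DCC, with no new visits. This assumes that the urine ratios and serum values are on the laboratory and event forms entered there (VII.E). If the DSMB keeps the AE grade, symptom status must also be on the event form.

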Subjects who have a subsequent elevated urine Ca:Cr that is a lower ratio than the initial measurement will remain on the study medication and no further action will be required. If the ratio of any subsequent spot urine is greater than the initial ratio, the woman will be asked to stop study medication, and be reminded to properly hydrate. She will be asked to return to the clinical center where blood will be drawn to determine serum Ca and 25(OH)D levels, no repeat urine is required at this time. If the levels of both are within the normal range, the subject will resume study medication and continue to be monitored per protocol each month (with any other elevated ratio again being compared to the initial elevated ratio). If either of the serum values are outside of the normal range, the procedure outlined above will be followed.

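### Hypercalciuria is only partly captured in the adverse-event count: the confirming urine is taken off the study pills, and later elevations require no confirming urine

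*Supplement*

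**What the plan says.** All references are to the current protocol.

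- **VI.G (urinary ratios)** describes the ratio as the first warning of toxicity and sets the elevated level at 1.55 on the mmol scale, or 0.55 mg/mg. At a first elevation: "She will be asked to stop the study medication and to return for a repeat evaluation after being instructed to increase her fluid intake". The repeat is meant to distinguish dehydration from true hypercalciuria. Then: "If the repeat test is normal she will resume the study medication and continue in the study". Only a repeat that stays raised leads to serum calcium and 25(OH)D.
- **VII.I (safety monitoring)** gives the same order: "Whenever any patient exceeds the caution limit, the study medication will be temporarily discontinued". Only the first elevation triggers a repeat urine. A woman whose later elevation is lower than her first "will remain on the study medication and no further action will be required". If it is higher, the pills are stopped and blood is drawn, but "no repeat urine is required at this time".
- **VII.J (adverse events)** counts hypercalciuria when the ratio is at least 1, with no unit, on a repeat, and excludes the rest: "If ratio normalizes after hydration this is NOT an adverse event". AEs and SAEs go to the DSMB by masked group.
- **VII.K (interim analyses)** links possible early termination on safety grounds to AE rates in the two arms.
- **VIII, Protection against Risks**, starts a case study and notifications when the ratio passes 1.55 mmol/mmol, with no repeat condition and no exemption for later elevations.

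**The concern.** Two changes are made at once before the confirming urine: the pill is withdrawn and fluids go up. If the ratio falls, either could be the cause, yet VII.J treats the fall as showing that no event occurred. Withdrawing placebo cannot lower the ratio, whereas withdrawing vitamin D might. The filter could therefore act differently in the two arms, and against the arm where an effect would be sought.

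The second gap is recurrence. VII.J needs a repeat measurement, and VII.I asks for none after the first elevation. A woman with raised ratios month after month can thus contribute nothing to the count.

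This ratio is the only laboratory safety measure taken monthly, and no table of unconfirmed or recurrent elevations by arm is planned. What is at stake is the DSMB's view of a between-arm difference in an early safety marker. The primary efficacy analysis is not affected.

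**Working it through.** The plan gives no hypercalciuria rate and no power for this comparison, so there is no stated figure to reproduce. The check follows the rules through and then shows a range under assumed rates.

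**1. Path of each elevation**

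| Situation | Handling (VI.G, VII.I) | Repeat urine? | Meets VII.J as written? |
|---|---|---|---|
| First elevation, repeat normal | pills stopped, fluids, repeat, resume | yes, off pills | no, excluded |
| First elevation, repeat still raised | as above, then serum tests | yes, off pills | yes |
| Later elevation, lower than the first | stays on pills | none required | no planned route |
| Later elevation, higher than the first | pills stopped, serum tests | none required | no planned route |

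No interval between stopping and the repeat is set.

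**2. Constructed example (mmol scale).** Take monthly ratios 2.9 (repeat 0.9), 2.8, 2.7, 2.6, 2.5. The smallest monthly value is 2.5/1.55 = 1.61 times the limit. The repeat is normal and every later value is below 2.9. The result is no hypercalciuria AE by the VII.J wording, no serum test triggered by a ratio, and no interruption after the first. A woman with 1.56 and later 1.60 is stopped and has blood drawn. The example shows what the rules permit, not how often it happens.

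**3. Share of elevated samples with no repeat.** With k monthly samples and an independent elevation probability p per sample, the share is 1 − [1 − (1 − p)^k]/(kp). Assumed k = 5 to 7 and p = 1% to 10%:

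- k = 5, p = 0.01: 0.02
- k = 7, p = 0.10: 1 − 0.522/0.70 = 0.255

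The range is about 2% to 26%. Clustering within women would raise it.

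**4. Effect on the by-arm comparison (all rates assumed).** There are 435 women per arm (section VIII) and a two-sided 0.05 test. Power = Φ[(d − 1.96·se0)/se1], where d is the difference in rates, se0 = √[2p̄(1 − p̄)/435] and se1 = √{[p1(1 − p1) + p2(1 − p2)]/435}. First elevations are 5% control and 10% active, and half persist on repeat in both arms before any off-pill effect.

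| Counted | Control | Active | RR | Power |
|---|---|---|---|---|
| Every first elevation | 5% | 10% | 2.0 | 0.80 |
| Persistent only, no off-pill effect | 2.5% | 5% | 2.0 | 0.49 |
| Stopping normalizes a further 25% of active cases | 2.5% | 5% × 0.75 = 3.75% | 1.5 | 0.18 |
| Stopping normalizes a further 50% of active cases | 2.5% | 5% × 0.50 = 2.5% | 1.0 | no difference to detect |

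First row: se0 = 0.01786, se1 = 0.01778, (0.05 − 1.96 × 0.01786)/0.01778 = 0.84, Φ = 0.80.

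**5. Units.** With molar masses 40.08 (calcium) and 113.12 (creatinine), 0.55 mg/mg × 113.12/40.08 = 1.55 mmol/mmol, so the two limits in VI.G agree. The 1 in VII.J matches neither: 1 mmol/mmol is 0.354 mg/mg, and 1 mg/mg is 2.82 mmol/mmol. Read as mmol/mmol, a repeat from 1.0 up to just under 1.55 would be an AE while below the caution limit.

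**The case against.** The strongest reply is that the ratio is a screen, not the toxicity. VII.I names hypercalcemia as the only known toxicity of excess vitamin D, and that stays reportable: asymptomatic hypercalcemia is an AE, and symptomatic hypercalcemia or raised 25(OH)D is an SAE. VII.H regards dehydration as a commoner cause of a raised ratio, so confirming a spot urine before calling it an event is defensible. The change log shows that the AE list and urine monitoring were shaped by the DSMB, and that the revised elevated-ratio procedure had its approval; the rule for later elevations is logged as a Steering Committee decision. Every woman has a 25(OH)D draw scheduled at 32–38 weeks, section VIII has its own trigger above 1.55 mmol/mmol, and the monthly ratios are on file.

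These points stand, and they rule out two stronger inferences that a reader might draw. One is that hypercalciuria is removed from the AE count altogether. It is not, since a first elevation that persists is counted. The other is that a recurrence can never be an AE. The list is introduced with "Adverse Events (AEs) will include (but not limited to", and not requiring a repeat urine does not forbid one.

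The reply does not close the gap. The scheduled draw does not include serum calcium, ratio-triggered serum tests miss normalized first elevations and lower recurrences, section VIII does not give the DSMB a by-arm count, and nothing requires the raw ratios to reach the DSMB by group.

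**Conclusion.** The point holds in a limited form. Only first elevations that persist after hydration and off the study pills have a planned route into the hypercalciuria count. The by-arm comparison therefore loses events, and a normal repeat does not answer the question that VI.G sets for it.

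A reader might go further and conclude that the comparison is biased toward no difference. The documents do not support that as a fact. It requires that stopping the active pill lowers the ratio before the repeat is taken, and the plan gives neither the interval, nor an off-pill normalization rate, nor rates by arm. If stopping has no effect in that time, the relative risk is undistorted and only power is lost (0.80 to 0.49 in the illustration). If it has an effect, the relative risk is pulled down (2.0 to 1.5 or 1.0). The true size cannot be derived.

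Separately, three sets of passages conflict on their face: the blanket interruption in VII.I and the trigger in section VIII against the no-action rule for lower recurrences; the purpose of the repeat against its being taken off the pills; and the unitless 1 in VII.J against 1.55 mmol/mmol.

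**What to change.** 1. Add a DSMB table by masked group of all monthly ratios at or above the caution limit, whatever their AE status: first, recurrent and unconfirmed. Give the number of women with at least one and with two or more elevations, the repeat result, and whether the repeat was taken on or off study pills.
2. State in VII.J that the exclusion of normalized ratios does not apply to this table.
3. Reconcile the three sets of conflicting passages named in the verdict. Which handling rule and which cut-off apply is for the sponsor and the DSMB.

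The cost is some AE wording and one table built from data already collected. The downside is a longer list of events in both arms, many of them benign.
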